### Aims of the study

In the second phase of BEST (BEST-2) the primary question will be: ‘Is daily oral azithromycin non-inferior (within a 20% margin) to oral amoxycillin-clavulanate at achieving resolution of exacerbations by day 21 of treatment?’

The secondary aims are similar to those in BEST-1 [32], and are to: 1) determine the effect of azithromycin or amoxycillin-clavulanate on QOL, systemic inflammation, time to next respiratory exacerbation, and duration of exacerbations; 2) examine factors that predict response to the two antibiotics, including respiratory pathogens (viruses, bacteria, macrolide-resistant bacteria) present in respiratory secretions, and systemic markers of inflammation; and 3) describe, by using sensitive molecular detection techniques, the point prevalence and diversity of respiratory viruses and *Mycoplasma pneumoniae* and *Chlamydiales* species during exacerbations, compared with the findings at enrolment when the children are clinically stable.

The study will test the primary hypothesis that oral azithromycin is non-inferior (within a 20% margin) to oral amoxycillin-clavulanate at achieving resolution of respiratory exacerbations by day 21 of treatment in children with non-CF bronchiectasis.

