### Sample size

We plan to enroll 170 children (85 per arm), providing 90% power (α = 0.05, 1-sided) with 20% non-inferiority margin to detect 80% resolution rate by day 21. The margin selected is relatively large in statistical terms, but the physicians considered it clinically appropriate. As the primary outcome will be obtained in all enrolled children, retention fraction has not been factored in for the intention-to-treat analysis.

The main secondary outcome (secondary aim 1) is PC-QOL. Based on a non-inferiority limit of 0.9 (minimum important difference [57]) and standard deviation of 0.9, our sample size provides a power of 99.9% (α = 0.05, one-sided 95% CI) for data from at least 136 children (assuming at least 80% retention of children enrolled). For secondary aim 2 (see list under ‘Aims of the study’), we will be examining eight main factors, and thus a sample size of 136 exceeds the recommended minimum (n = 10 per factor) [65]. The eight factors are: smoking, age, underlying etiology, detection of virus (any versus none, then single versus multiple viruses), presence of azithromycin resistance, and levels of various blood markers (IL-6, IL-10, IP-10).

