#### Statistical analysis for secondary outcomes and aims

For the clinical secondary outcome (secondary aim 1), the *t*-test or the Mann–Whitney test will be used for continuous variables (depending on normality of data distribution). A Kaplan-Meier curve will be constructed for each group for time to resolution and time to next exacerbation, as reported previously [67]. For secondary aim 2 (factors that predict response to antibiotics), univariate analyses will be used to examine several biologic factors (for example, smoking, age, ethnicity, underlying etiology, detection of virus (any versus none, then single versus multiple viruses), presence of azithromycin resistance, and levels of blood markers (IL-6, IL-10, IP-10)). Factors with *P*<0.2 will be included in a logistic regression model. Potential interactions (for example,. between viruses and bacteria) will be examined in the model. Descriptive data will be used for secondary aim 3 (point prevalence of respiratory pathogens).

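### Aim 2 asks what predicts response to the two antibiotics, but its pooled, screened model names neither treatment arm nor a treatment-by-factor interaction, so a drug-dependent effect of azithromycin resistance is averaged over the arms

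*Protocol article*

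**What the plan says.** Under Aims of the study, secondary aim 2 is to "examine factors that predict response to the two antibiotics, including respiratory pathogens (viruses, bacteria, macrolide-resistant bacteria) present in respiratory secretions", together with systemic markers of inflammation.

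The Sample size section sizes this aim: "we will be examining eight main factors, and thus a sample size of 136 exceeds the recommended minimum (n = 10 per factor"). The 136 comes from the sentence before, on PC-QOL: "for data from at least 136 children (assuming at least 80% retention of children enrolled"). The list that follows is worded as complete: "The eight factors are: smoking, age, underlying etiology, detection of virus (any versus none, then single versus multiple viruses), presence of azithromycin resistance", and then IL-6, IL-10 and IP-10.

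The section on statistical analysis for secondary outcomes and aims gives the method: "univariate analyses will be used to examine several biologic factors (for example, smoking, age, ethnicity, underlying etiology" and the other factors). Those with P "<0.2 will be included in a logistic regression model". On interactions it says: "Potential interactions (for example,. between viruses and bacteria) will be examined in the model".

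Under Intervention and follow-up, both arms receive an active antibiotic plus the placebo of the other. No arm is untreated.

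**The concern.** The aim is about response to two named drugs. In this design, what randomization can show about a particular drug is whether a factor relates to resolution differently in the two arms. The stated method does not ask that. Arm is absent from the list of eight, the 136 children come from both arms, the screen is univariate, and the one interaction given as an example is between viruses and bacteria.

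This matters most for azithromycin resistance, whose effect would be expected to depend on whether the child received azithromycin. In a pool where about half the children received the other drug, an arm-dependent effect is averaged. If the averaged effect misses P<0.2, the factor leaves the analysis before any interaction could be looked at. The report could then say that resistance does not predict response, although the arm-specific question was never put.

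**Working it through.** **The plan's own figure.** 0.80 × 170 = 136, and 8 factors × 10 = 80, which is below 136. The figure reproduces. Because 136 is 80% of the whole trial (85 per arm), it implies one analysis over both arms, about 68 children from each.

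**Inputs for the dilution.** Equal arms and 80% resolution are the planning values in the Sample size section. The documents give neither the prevalence of azithromycin resistance nor its effect. I assume 55% resolution in azithromycin recipients who carry resistant bacteria and 80% in susceptible children in either arm. I then vary the figure for resistant children on amoxycillin-clavulanate.

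**Risk difference.** The azithromycin-arm effect is 0.80 − 0.55 = 25 points. With equal arms, pooled resolution in resistant children is (0.55 + a)/2, where a is their resolution on amoxycillin-clavulanate.

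| a | Pooled, resistant | Pooled difference | Share of the 25 points |
|---|---|---|---|
| 80% (no effect) | 67.5% | 12.5 | 0.50 |
| 75% | 65.0% | 15.0 | 0.60 |
| 70% | 62.5% | 17.5 | 0.70 |
| 55% (same effect in both arms) | 55.0% | 25.0 | 1.00 |

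**Odds ratio when a = 80%** (susceptible versus resistant). Azithromycin arm: (0.80/0.20)/(0.55/0.45) = 3.27. Pooled: (0.80/0.20)/(0.675/0.325) = 1.93. On the log scale the pooled effect is 0.55 of the arm-specific one.

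**Does a treatment main effect help?** Hardly. In expected-value logistic models with 60% or 40% resolution under resistance on azithromycin, no effect on amoxycillin-clavulanate and 20% or 40% prevalence, the pooled log odds ratio is 0.55 of the azithromycin-arm value without arm and 0.55 to 0.57 with it. Only an arm-by-resistance term or separate estimates by arm recover the arm-specific effect.

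**The screen.** Take a = 80% and resistance prevalence q, and let P<0.2 in the expected direction mean z > 1.2816. Then SE = √[0.675 × 0.325/(136q) + 0.80 × 0.20/(136(1 − q))].

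At q = 20%:
- Pooled: SE = √(0.2194/27.2 + 0.16/108.8) = 0.0977, z = 0.125/0.0977 = 1.28, chance of passing 50%.
- Azithromycin arm alone (68 children): SE = √(0.2475/13.6 + 0.16/54.4) = 0.145, z = 0.25/0.145 = 1.72, chance 67%.
- Interaction (difference between the arms in risk difference): SE = √(0.02114 + 0.16/13.6 + 0.16/54.4) = 0.189, z = 1.32, chance 52%.

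| Resistance prevalence | Pooled, 136 | Azithromycin arm, 68 | Interaction, same threshold | Interaction, two-sided 0.05 |
|---|---|---|---|---|
| 10% | 37% | 49% | 38% | 16% |
| 20% | 50% | 67% | 52% | 26% |
| 30% | 58% | 77% | 60% | 33% |

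If a = 70%, the pooled screen passes with probability 50%, 68% and 77%, about equal to the azithromycin-arm analysis, so the screening loss disappears. The pooled estimate (17.5 points) would still not be the effect in either arm (25 and 10).

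**The case against.** Several objections stand and limit the point.

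- **A reader might infer that the pooled model finds only predictors of natural resolution.** The documents do not support this. Every child receives an active antibiotic, so the model estimates predictors of resolution under treatment. Prognostic and drug-specific effects are mixed. They are not reduced to natural history.
- **A reader might take the halving as a property of the plan.** It is conditional. It needs equal arms and no association between resistance and resolution on amoxycillin-clavulanate, and the article states nothing about that association.
- **The analysis section is open.** Both its factors and its interactions are introduced as examples, and its list is of biologic factors, so arm-by-resistance is not excluded. A condensed article may leave the full list of interactions to another document. This weakens any claim that the plan forbids such a term. It does not remove the point: the list under Sample size is closed, and a pooled univariate screen comes before the model in which interactions are examined.
- **The screening percentages do not show a power gain.** At the same threshold the interaction test does about as well as the pooled screen (52% against 50% at 20% prevalence). The low chances come largely from few resistant children. The gain from the change is an estimate that answers the aim and cannot be dropped.
- **Response to antibiotics can be read loosely** as clinical response among treated children. On that reading the pooled model is adequate, but the aim refers to the two antibiotics and names macrolide-resistant bacteria.

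The aim is secondary. The primary comparison and PC-QOL are untouched.

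**Conclusion.** The concern holds in a limited form. The stated method for aim 2 pools both arms, screens univariately and names no treatment term or treatment-by-factor interaction. Its estimates are averages over two drugs and do not show what predicts response to each.

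For azithromycin resistance, the pooled risk difference is half the azithromycin-arm effect if resistance does not matter under amoxycillin-clavulanate. The share rises to 0.60 and 0.70 if resistant children resolve in 75% or 70% there, and to 1.00 if the effect is the same in both arms. These sizes rest on my assumed 55% and on equal arms. That both arms are pooled is inferred from the 136 children and the single model.

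The improvement is cheap and concerns interpretation more than power.

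**What to change.** Before unblinding, state for aim 2 that:

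1. azithromycin resistance stays in the analysis whatever its result at the P<0.2 screen;
2. its association with resolution is reported separately by arm, with confidence intervals, from a model containing arm, resistance and arm-by-resistance;
3. this analysis is exploratory;
4. factors without a treatment interaction are described as predictors of resolution, not of response to a particular antibiotic.

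The cost is analysis wording and two extra terms, with no further children, visits or data. Ten terms at 10 children each need 100, still below 136 by the plan's own rule. By outcome events the model is already thin: 20% of 136 is about 27 non-resolved children, or 3.4 per factor for eight and 2.7 for ten.

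The interval for the interaction will be wide. At 136 children and two-sided 0.05, power on the log-odds scale is about 16% to 22% for 60% against 80% resolution on azithromycin, and 43% to 58% for 40% against 80%. Both ranges are for resistance prevalences of 20% to 40%, with no effect under amoxycillin-clavulanate. A non-significant interaction must therefore not be reported as evidence that resistance is irrelevant.

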### Statistical analysis and reporting

Data will be reported and presented in accordance with the updated Consolidated Standards of Reporting Trials (CONSORT) criteria [66]. Children will be analyzed in accordance with allocation status (regardless of subsequent management).

For our primary aim, the main effects of the interventions will be determined by comparing the primary outcome (resolution of exacerbation) between groups (azithromycin versus amoxicillin-clavulanate). Children who exit the study as ‘clinically worse’ or ‘drop-out’ before the end point is reached will be considered as ‘non-resolved’. Those who exit the study as ‘returned to baseline’ will be considered as ‘resolved’. Odds ratios will be calculated and, if appropriate, the number needed to treat (for benefit) will be expressed. Per-protocol analysis will be an *a priori* secondary analysis.

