### Outcome measures

#### Primary outcome

The primary outcome will be the proportion of children whose exacerbations have resolved by day 21 of treatment. Exacerbations will be considered resolved when symptoms and signs are the same as the baseline state. Children who are withdrawn from the study, or receive additional antibiotic treatment, will be categorized as non-resolved.

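### The effect measures named for the primary aim (odds ratio, number needed to treat for benefit) are not on the absolute risk-difference scale of the 20% non-inferiority margin

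*Protocol article*

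**What the plan says.** The hypothesis in Aims of the study is that "oral azithromycin is non-inferior (within a 20% margin) to oral amoxycillin-clavulanate at achieving resolution of respiratory exacerbations by day 21". Under Primary outcome the endpoint is binary: "The primary outcome will be the proportion of children whose exacerbations have resolved by day 21 of treatment".

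The Sample size section applies the same margin to that proportion. The total is 170, split equally between the arms, with power put at 90% and a one-sided alpha of 0.05; the calculation is described as made "with 20% non-inferiority margin to detect 80% resolution rate by day 21". Later, the Discussion defends the size of the margin again.

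Statistical analysis and reporting says that the primary outcome will be compared between the two groups. It then names the effect measures: "Odds ratios will be calculated and, if appropriate, the number needed to treat (for benefit) will be expressed". No risk difference is named there, no confidence limit is tied to the margin, and no odds-ratio margin appears anywhere in the article.

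**The concern.** A non-inferiority conclusion rests on one comparison: a confidence limit for the treatment effect against the margin, both on the same scale. Here the margin sits on the scale of the proportion resolved, and the named measures do not match it.

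- **Odds ratio.** It is on a different scale. Turning 20 points into an odds ratio needs a control rate, and the analysis section fixes none. The answer moves substantially over plausible control rates.
- **Number needed to treat.** It is the reciprocal of a risk difference, so it is at least an absolute measure. It is offered only for benefit, though, which presumes that azithromycin resolves more exacerbations. The design asks whether azithromycin is not much worse.

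What is at stake is the trial's main conclusion. If the scale, or the control rate used for conversion, is settled after the data are seen, the same data can support either verdict.

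**Working it through.** **Inputs.** From Sample size: 85 per arm, 80% resolution (taken as equal in both arms), 20% margin, 90% power, alpha 0.05 labelled one-sided, no allowance for dropout. The article writes 20% without saying whether it is absolute or relative, so both readings were tried.

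**Step 1: reproduce the sample size on the risk-difference scale.**
n per arm = [p(1-p) + p(1-p)] × (z_alpha + z_power)² / margin², with p = 0.80 and margin = 0.20, so n = 0.32/0.04 × (z_alpha + z_power)² = 8 × (z_alpha + z_power)².

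- One-sided 0.025: 8 × (1.960 + 1.282)² = 84.06, so **85 per arm, 170 in total**. This is an exact match, with 90.3% power at 85.
- One-sided 0.05, as printed: 8 × (1.645 + 1.282)² = 68.5, so **69 per arm, 138 in total**. Power at 85 is 94.7%.

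**Step 2: try other readings (per arm, one-sided 0.05 / 0.025).**

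| Margin reading | 0.05 | 0.025 |
|---|---|---|
| Absolute 20 points, unpooled variance | 69 | **85** |
| Absolute 20 points, Farrington-Manning | 71 | 87 |
| Absolute 20 points, continuity-corrected | 79 | 94 |
| Relative 20% (0.2 × 0.80 = 16 points) | 108 | 132 |
| Odds-ratio margin 0.375 | 112 | 137 |

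Only the absolute reading lands on 85. The relative and odds-ratio readings need at least 108.

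**Step 3: convert the margin to an odds ratio.**
OR at the margin = [(p - 0.2)/(1.2 - p)] / [p/(1 - p)], where p is the control rate.

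| Control rate | OR equal to a 20-point deficit |
|---|---|
| 90% | 0.259 |
| 80% | 0.375 |
| 70% | 0.429 |
| 60% | 0.444 |

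In the other direction, a fixed odds ratio of 0.375 means 23.3 points at a 70% control rate, 20.0 at 80% and 12.9 at 90%.

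**Step 4: can the scale change the verdict?** Take 70/85 (82.4%) resolved on azithromycin and 77/85 (90.6%) on amoxycillin-clavulanate, with Wald limits.

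- Risk difference = 0.8235 - 0.9059 = -0.0824. SE = √(0.8235 × 0.1765/85 + 0.9059 × 0.0941/85) = 0.0521. Lower 95% limit = -0.0824 - 1.96 × 0.0521 = **-18.4 points**, above -20, so non-inferior.
- Odds ratio = (70 × 8)/(77 × 15) = 0.485. SE of log OR = √(1/70 + 1/15 + 1/77 + 1/8) = 0.468. Lower 95% limit = exp(ln 0.485 - 1.96 × 0.468) = **0.19**, below 0.375, so not non-inferior.

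The split does not depend on the confidence level: with a one-sided 95% bound the limits are -16.8 points (passes) and 0.225 (fails). It also remains if the margin is converted at the observed control rate. Twenty points below 77/85 is 60/85, and (60/25)/(77/8) = 0.249, still above both odds-ratio limits.

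**The case against.** The strongest reply is that the analysis section never calls the odds ratio the primary estimate or the decision criterion. It says that resolution will be compared between groups, and resolution is defined as a proportion, so a risk difference is compatible with the text. A condensed article can leave the decision rule to a full protocol or SAP. All of that stands, and the absence of a rule is not by itself the point. What remains is that the article does name effect measures for this aim, and they are off the margin's scale.

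Three stronger readings are tempting and are not supported:

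- **That an odds ratio cannot be compared with the margin at all.** It can once a control rate is fixed: 0.375 at the planned 80%. Likewise a 20-point difference is a number needed to treat of 1/0.20 = 5. The comparison is indirect, not impossible.
- **That the margin would never be applied.** The hypothesis, the sample size and the Discussion all keep it.
- **That a non-significant odds ratio would be taken as non-inferiority.** With 58/85 versus 68/85 resolved, the odds ratio is 0.54 (95% CI 0.27 to 1.08) and the lower risk-difference limit is -24.8 points. This misleads only if the margin is ignored, because the odds-ratio limit of 0.27 also fails 0.375. Nothing in the article says that non-significance would count as non-inferiority.

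It can also be said that the absolute reading is inferred and that the exact match needs one-sided 0.025 rather than the printed 0.05. Both are true. A route that keeps 0.05 and allows for 80% retention comes close (68.5/0.8 = 85.6, so 86), but the section says that "retention fraction has not been factored in for the intention-to-treat analysis". That route also uses the absolute scale, so the conflict concerns the error rate and leaves the scale untouched.

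**Conclusion.** The point holds in this form: the effect measures named for the primary aim do not match the scale on which the trial was sized. The equivalent odds ratio ranges from 0.26 to 0.43 as the control rate goes from 90% to 70%, and at 85 per arm there are plausible results for which the two scales give opposite verdicts.

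This rests on reading 20% as absolute points, which the sample size supports and a relative margin does not reproduce; on equal 80% resolution in both arms for the sample-size check; and on Wald intervals for the illustration. The article does not exclude a risk-difference analysis in documents not shown, so the finding concerns what the published text fixes and does not show that the trial will be analysed wrongly.

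**What to change.** In Statistical analysis and reporting, state that:

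1. The primary estimate is the risk difference in resolution by day 21, azithromycin minus amoxycillin-clavulanate, with its confidence interval.
2. Non-inferiority is concluded only if the lower confidence limit is above -20 percentage points.
3. Odds ratios are supportive. The number needed to treat for benefit is dropped from the primary analysis.
4. The confidence level is given explicitly and agrees with Sample size. A two-sided 95% interval (one-sided 0.025) fits 85 per arm at 90% power. The printed one-sided 0.05 would need 69 per arm, and 85 would then give 94.7% power. The authors should say which applies and correct the other statement; the level should not change unannounced through the wording of the interval.

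The cost is a few sentences, with no extra data and no change to the 170 children. If the SAP already specifies this, only the article's text needs aligning. If not, the change should be made before unblinding.

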#### Statistical analysis for secondary outcomes and aims

For the clinical secondary outcome (secondary aim 1), the *t*-test or the Mann–Whitney test will be used for continuous variables (depending on normality of data distribution). A Kaplan-Meier curve will be constructed for each group for time to resolution and time to next exacerbation, as reported previously [67]. For secondary aim 2 (factors that predict response to antibiotics), univariate analyses will be used to examine several biologic factors (for example, smoking, age, ethnicity, underlying etiology, detection of virus (any versus none, then single versus multiple viruses), presence of azithromycin resistance, and levels of blood markers (IL-6, IL-10, IP-10)). Factors with *P*<0.2 will be included in a logistic regression model. Potential interactions (for example,. between viruses and bacteria) will be examined in the model. Descriptive data will be used for secondary aim 3 (point prevalence of respiratory pathogens).

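### Secondary aim 2 screens factors at P<0.2 and estimates the survivors on the same children, so their estimates and intervals ignore the selection; the two factor lists also differ (eight against nine)

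*Protocol article*

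**What the plan says.** The Aims section makes it a secondary aim to "examine factors that predict response to the two antibiotics, including respiratory pathogens (viruses, bacteria, macrolide-resistant bacteria) present in respiratory secretions", together with systemic markers of inflammation.

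The Sample size section justifies this aim by a count: "we will be examining eight main factors, and thus a sample size of 136 exceeds the recommended minimum (n = 10 per factor"). It then lists them: "The eight factors are: smoking, age, underlying etiology, detection of virus (any versus none, then single versus multiple viruses), presence of azithromycin resistance", followed by three blood markers (IL-6, IL-10, IP-10). That makes eight, and ethnicity is not among them.

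The section on statistical analysis for secondary outcomes and aims gives the method: "univariate analyses will be used to examine several biologic factors (for example, smoking, age, ethnicity, underlying etiology, detection of virus" and so on through the same resistance and blood-marker items. This list has nine named factors and is worded as examples. The model-building rule follows, with interactions added without a number: "Factors with *P*<0.2 will be included in a logistic regression model. Potential interactions (for example,. between viruses and bacteria) will be examined in the model".

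No significance level is given for the final model of aim 2. The alphas in the article belong to the primary outcome and to PC-QOL.

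**The concern.** A factor reaches the final model only if it already looked associated in these children. The model then treats its coefficient as though it had been chosen in advance. For a factor with no effect, the interval among reported factors misses zero too often. For a factor with a modest effect, the samples in which it is reported are those in which it came out large. Factors that fail the screen drop out of the model.

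The reported predictors, such as azithromycin resistance, virus detection or a blood marker, are what readers would carry into later studies. Their size and precision would be misstated.

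The second issue is consistency. The sample-size argument rests on a count of eight, and the analysis section describes a longer, open list for the same aim.

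**Working it through.** **Inputs.** From the Sample size section: 170 children, 80% retention, 80% resolution, eight factors, a minimum of 10 children per factor. From the analysis section: nine named factors and the P<0.2 rule. Assumed, because the article does not give them: resolution by day 21 as the modelled outcome, a final two-sided level of 0.05, factor prevalences, and latent correlations among the factors.

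**1. The plan's own figure.** 0.80 × 170 = 136, and 136/8 = 17 children per factor, above 10. With ethnicity, 136/9 = 15.1, still above 10. If both virus codings are tested, the eight become nine contrasts and the nine become ten: 136/10 = 13.6.

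**2. Events.** For a logistic model the scarcer outcome limits the information. 136 × 0.20 = 27.2 non-resolved, so 27.2/8 = 3.4 per factor, 27.2/9 = 3.0, and 27.2/10 = 2.7 per contrast. The plan's check counts children, not events.

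**3. Interval coverage for null factors that pass the screen.** In the simplest case one factor is screened and then refitted alone. A null P value is uniform, so P(P<0.05 | P<0.2) = 0.05/0.20 = 25%, and the 95% interval covers 75%. With several factors in the model (136 children, 20% non-resolved, 1,500 null trials per setting), the rejection rate among selected factors was:

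| Latent correlation | Rejection among selected | Coverage = 1 − rejection |
|---|---|---|
| 0 | 21% | 79% |
| 0.3 | 17% | 83% |
| 0.5 | 11-12% | 88-89% |

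A separate run with ten terms and its own assumed prevalences gave 77-92%. A Firth fit of all ten terms, reporting every factor, covered about 96%.

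**4. Overstatement of a modest true effect.** Take a standardised continuous factor with true log-odds 0.30.
- SE ≈ 1/√(136 × 0.2 × 0.8) = 1/√21.76 = 0.214.
- Expected z = 0.30/0.2144 = 1.399; the screen requires |z| > 1.282.
- Chance of passing ≈ 0.547 + 0.004 = 0.551.
- Mean z given passing = [1.399 × 0.551 + φ(0.118) − φ(2.681)]/0.551 = (0.770 + 0.396 − 0.011)/0.551 ≈ 2.10.
- Mean reported log-odds ≈ 2.10 × 0.214 = 0.45, or 1.5 times the truth.

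The simulation with independent factors gave 0.47 (0.47/0.30 = 1.6 times), against 0.29 from the full Firth fit.

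**5. Chance of at least one false predictor, no true predictor.** For k independent tests, 1 − 0.95^k is 33.7% for k = 8, 37.0% for k = 9 and 40.1% for k = 10. By simulation at 136 children and 80% resolution:

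| Procedure | 8 factors, correlation 0 / 0.3 / 0.6 / 0.8 | 10 contrasts, same correlations |
|---|---|---|
| Screened as planned | 31 / 27 / 19 / 13% | 37 / 32 / 22 / 16% |
| All in one unpenalised model | 34 / 34 / 34 / 31% | 40 / 40 / 39 / 39% |
| Univariate tests only | 32 / 30 / 29 / 27% | 37 / 36 / 33 / 30% |

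A full Firth fit of ten terms gave 31-32%. One virus-by-resistance interaction added about 1-2 points to the screened figures.

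**The case against.** The strongest reply is that the screen does not cause false predictors, and this is right. A reader might infer that the P<0.2 rule produces the 15-40% family-wise rate. Step 5 shows the screened rate at or below that of the full unpenalised model, and Firth does not remove it either. The rate comes from the number of uncorrected tests, and it also needs a 0.05 decision rule that the article does not state for this aim.

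Two further inferences also fail. The 11-21% rejection rate among selected factors is conditional on passing the screen. Unconditionally, about 20% of null factors pass, so the per-factor false-positive rate is about 0.20 × 0.21 = 4% down to 0.20 × 0.11 = 2%, below 5%. Nor can one say that any given significant predictor is probably due to chance: a rate computed with no true predictor does not give that probability.

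Multiplicity rules, an exploratory label and named interactions may reasonably sit in an analysis plan that is not shown, so their absence here is no error. The list difference is also small. It is one variable, both virus codings appear in both sections, a count of main factors need not exclude others, and 136/9 still passes the stated check.

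The screening rule itself survives these points. It is stated as a commitment, and the conditional coverage in step 3 is the relevant quantity for intervals that are reported only after selection.

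**Conclusion.** The concern holds for the estimates and intervals of the factors that are reported, not as a claim that the screen inflates false discoveries. Nominal 95% intervals of null factors that pass cover about 77-92%. A modest true effect is overstated by up to about 1.6 times when factors are independent, and by less as correlation rises.

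These sizes rest on assumed prevalences and correlations, 136 children with complete factor data, and 20% non-resolved. The Specimen collection section obtains exacerbation swabs and blood only in a subset, so the real numbers could be smaller.

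The eight-against-nine difference is a consistency correction that changes no stated conclusion. Aim 2 is secondary, and the primary non-inferiority comparison is untouched.

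**What to change.** 1. Use one closed factor list in both the Sample size and the analysis sections. If ethnicity stays, correct the count to nine (136/9 = 15.1 children per factor, still above 10). State whether virus detection enters as one term or two.
2. Drop the P<0.2 screen. Fit all listed factors jointly by Firth or ridge logistic regression and report every estimate with its confidence interval. The coverage figure above was checked for Firth; if ridge is chosen, say how its intervals are obtained.
3. State that the results are hypothesis-generating. This sentence is needed because the penalised fit corrects the selection problem but leaves the family-wise rate at about 31-32% for ten terms at an assumed 0.05.

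The cost is a few changed sentences, slightly more analysis work and more modest claims for aim 2. No new children or data are needed.
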